### Outcome measures

Primary outcome measures will include the mean differences in the frequency/duration/related costs of high-cost mental health services utilization (i.e., volume and proportion of mobile crisis visits, ED visits, hospital admissions and readmissions and associated LOS for each admission) between one year pre- and post-assessment date for same patients at RASP (within-subject comparison) and between the IG (RASP) and CG (historical data) (between-subjects comparison). Other primary outcome measures will be the mean difference in the number and proportion of total referrals booked directly for a psychiatrist and the number of calendar days for access to psychiatrists, also compared to the control group.

Secondary outcome measures include the mean difference in the frequency/duration/related costs of high-cost health services utilization one year post for patients who access the RASP and participate in the Text4Support RCT (to receive either daily supportive text messages or a single text message with a link to e-mental health resources) and patients accessing RASP but who do not participate in the Text4Support RCT. Other secondary outcome measures include a descriptive summary of the sociodemographic and clinical characteristics of the assisted population, the mean scores on the Patient Health Questionnaire 9 (PHQ-9) [38], Generalized Anxiety Disorder 7 (GAD-7) [39], World Health Organization 5 (WHO 5 Well-Being Index) [40], Brief Resilience Scale (BRS) [41], Recovery Assessment Scale (RAS) [42], Adverse Childhood Experience (ACE questionnaire) [43], Brief Substance use Craving Scale (BSCS) [44], and the Columbia-suicide severity rating scale (C-SSRS) [45], as well as the prevalence of likely MDD, GAD and low resilience. Patient overall impressions (i.e. barriers to accessing RASP, satisfaction level, likely recommend the service to others, etc.) and impressions on the experience (i.e. feelings of welcomeness, respect, enough time to talk, the problem addressed, and understanding of treatment) are part of the patient satisfaction quantitative evaluation. An in-depth evaluation of healthcare partner impressions and patient satisfaction will be obtained through qualitative key informant interviews until saturation is reached and no new themes and subthemes emerge.

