### Sample size considerations

With two staff psychiatrists and a clinical coordinator, we expect an average of six patients to receive comprehensive psychiatric assessments at the RASP each working day. Thus, we anticipate that the total number of patients accessing the service over the 24-month data collection period would be at least 2500. We also expect the sample size for the control population (patients whom a primary care provider referred to the MHAP Central Intake Services between May 2020 and May 2022) to be at least equal to the numbers seen at the RASP over a similar two-year time frame. Therefore, the data set to be generated from an overall sample of 5000 patients in this study would be large. With the assumption that the implementation of RASP will lead to at least a 10% reduction in high-cost health services utilization one-year post initial referral from a primary care provider for patients attending the service compared to patients who were offered a future appointment to see a mental health clinician as an entry point to the community mental health program, a power of 90% (β = 0.1) and a two-sided significance level of α = 0.05, and assuming an aggregated mean high cost health services utilization of 10 (SD =1) for the control population, we estimated that a sample size of 525 per group would be sufficient. Given that we expect at least 2500 patients per group in our study, it is highly probable that our study has more than sufficient power to detect the projected differences in high-intensity/cost health services utilization between the two groups.

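### About 15 comparisons are called primary with no ranking, while the only sample size rests on an undefined aggregate that is not among them

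*Protocol article*

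**What the plan says.** Under Outcome measures, the article states "Primary outcome measures will include the mean differences in the frequency/duration/related costs of high-cost mental health services utilization" and spells this out as "volume and proportion of mobile crisis visits, ED visits, hospital admissions and readmissions and associated LOS for each admission". Each measure is to be compared twice: before and after the RASP assessment in the same patients, and "between the IG (RASP) and CG (historical data) (between-subjects comparison"). The same section continues: "Other primary outcome measures will be the mean difference in the number and proportion of total referrals booked directly for a psychiatrist", together with "the number of calendar days for access to psychiatrists, also compared to the control group". None of these is singled out or placed above another. Study objectives adds a qualitative objective that is also called primary.

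Sample size considerations contains one calculation, for the between-group comparison only. It assumes a 10% reduction, 90% power and two-sided alpha 0.05, "assuming an aggregated mean high cost health services utilization of 10 (SD =1) for the control population". It arrives at 525 per group, expects at least 2500 per group, and concludes that power for differences in high-cost utilization is ample.

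The Quantitative analysis section then applies ANCOVA to the relevant utilization variable in each case, with the same variable from the year before as covariate. It names no aggregate.

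**The concern.** Two elements that the article itself fixes do not match. The list of primary outcomes names components (mobile crisis visits, ED visits, admissions, readmissions, length of stay, costs) and access measures. The sample size is for a single combined quantity. Nowhere does the article say how visits, admissions and days in hospital would be added together, or whether length of stay enters at all.

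Two things are at stake. First, the reassurance about power attaches to a variable that the study does not plan to report, and it cannot be carried over to rarer or more skewed components. Second, with no lead outcome and no statement of whether one, some or all of the measures must improve, a favourable result on any one of them could be presented as a primary success.

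**Working it through.** **1. Counting the primary comparisons (Outcome measures).** Utilization measures: mobile crisis visits, ED visits, admissions, readmissions and length of stay = 5. Adding related costs gives 6. Two comparisons each: 6 × 2 = 12. Access measures: number booked directly, proportion booked directly, days to access = 3. Total 12 + 3 = 15. The count would rise if volume and proportion of each service, or the two control periods given under Participants and data collection, were taken separately. Without the two cost comparisons it would be 13.

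**2. Reproducing the plan's own figure (Sample size considerations).** Inputs: control mean 10, 10% reduction so difference 1, SD 1, two-sided alpha 0.05, power 90%.

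n per group = 2 × (1.960 + 1.282)² × (SD/difference)² = 2 × 10.51 × 1 ≈ 21.0, rounded up to 22.

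The stated 525 is not reproduced. Changing to one-sided testing (18), 80% power (16) or 95% power (26) does not come near it. A standardized difference of 0.2 does: 2 × 10.51 × (1/0.2)² ≈ 525.4, or 526 when rounded up. With a difference of 1, that corresponds to an SD of about 5, not 1.

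**3. What 2500 per group can detect in a listed outcome.** For a 10% reduction in a mean, only the ratio CV = SD/mean matters. The largest CV that gives 90% power is

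0.1 / [(1.960 + 1.282) × √(2/2500)] = 0.1 / (3.242 × 0.02828) ≈ 1.09.

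Power at other values is Φ(0.1 / (CV × 0.02828) − 1.960):

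| CV (assumed) | Power at 2500 per group |
|---|---|
| 0.5 | >99.9% |
| 1.0 | 94% |
| 1.5 | 65% |
| 2 | 42% |
| 3 | 22% |

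The article gives no SD or rate for any component, so the CV column is an assumed range. The calculation compares unadjusted means; under ANCOVA the relevant SD is the residual one, which is smaller if the pre-year value is predictive. As an illustration, a Poisson count has CV = 1/√mean, so it passes 1.09 once its yearly mean falls below 1/1.09² ≈ 0.84, and overdispersion makes this worse. For a yes/no outcome with a 10% relative reduction, power at 2500 per group is 94% at a control rate of 50%, 44% at 20% and 23% at 10%.

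The assumed aggregate has CV = 1/10 = 0.1. Nothing in the article suggests that the components share that value.

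**4. Chance of at least one false positive.** Assume 15 tests, each two-sided at 0.05 and unadjusted, no true effect anywhere, and any one significant result taken as success. If independent: 1 − 0.95¹⁵ = 53.7%. Simulation with equally correlated normal test statistics gives:

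| Correlation | 15 tests |
|---|---|
| 0 | 54% |
| 0.5 | 36% |
| 0.7 | 26% |
| 0.9 | 14% |

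Without the two cost comparisons, the independent case is 1 − 0.95¹³ = 48.7%. The six between-group utilization and cost tests alone give 26%, 21% and 16% at correlations 0, 0.5 and 0.7.

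**The case against.** High-cost utilization is the common thread of the primary objective, the 10% hypothesis, the opening of the outcome list and the sample size, so the aggregate is not foreign to the study. That is fair, but the outcome list resolves the construct into components and the analysis treats them one by one. The combined quantity that was powered is never defined.

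A reader might infer that no listed outcome has 90% power. The article does not support that. The absence of a calculation is not the absence of power, and at 2500 per group any measure with SD/mean up to about 1.09 would reach 90% for a 10% reduction.

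A reader might also infer that the plan has a false-positive rate of 36% to 54%. That is not a property of the plan. It requires 15 unadjusted tests, a rule that any one suffices, and correlations no higher than 0.5. The article states no such rule. Its Hypothesis section expects the effect in both the within-subject and the between-subject comparison, which points away from accepting either alone. Readmissions are a subset of admissions, length of stay arises only from admissions, and costs derive from utilization, so strong correlation is likely and the lower figures may be nearer. The cost measures are to be handled in a cost-consequence analysis with bootstrapping, and may not be significance tests at all.

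Finally, a multiplicity method may stand in an analysis plan that is not shown, so its absence here is no finding. What remains is the mismatch between the outcome list and the basis of the sample size, both of which are stated in this article.

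**Conclusion.** The point holds as a mismatch between stated elements. About 15 quantitative comparisons are primary and unranked, and the only power calculation concerns an undefined aggregate that is neither listed as an outcome nor named in the analysis. The claim of ample power is therefore unsupported for every listed outcome. It may prove true for some and false for others, with the dividing line at an SD/mean of about 1.09 for a 10% reduction at 2500 per group. The within-subject and access outcomes have no calculation of any kind.

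The error-rate figures (54% down to 14% as correlation rises from 0 to 0.9) show what the lack of a lead outcome could cost under the conditions given with them. They do not describe a rule that the plan has adopted. The aggregate's own calculation also fails: its stated inputs lead to 22 per group, not 525, so it cannot serve as the anchor without being redone.

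**What to change.** Before results are examined:

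- Define the aggregate: which services count, over what period per patient, and whether days in hospital enter.
- Name it, for RASP versus control, as the single lead primary outcome, in the same words under Outcome measures, Sample size considerations and Quantitative analysis.
- Make the components, costs, within-subject changes and access measures secondary, or rank them explicitly.
- Restate the power for the lead outcome with an SD justified from data, correct the disagreement between the stated inputs and 525, and limit the power claim to that outcome.

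The cost is protocol wording and one recalculation, with no change to data collection or to the expected numbers. The price is that the other measures, including the within-subject and access results that a program evaluation may value highly, carry less formal weight. How any further adjustment among them is done can be left to the analysis plan.

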Similar concerns are related to frequent ED visits. Frequent ED visitors are commonly defined as people having 4 or more ED visits during the past 12 months [18], and they are more likely to suffer from chronic somatic diseases, drug and alcohol abuse and acute mental illness [18]. Predictors for recurrent ED visits due to acute mental health problems are usually substance abuse, single status and homelessness [19].

In addition to readmission rates and frequency of ED visits, length of stay (LOS) is another important quality of care indicator. LOS is defined as the number of days between admission and discharge dates for each admission experienced [20]. LOS is likely to be multifactorial, but some factors associated with longer LOS have been consistently identified: biological sex (being male), ethnicity (being Asian, Black, or having mixed background), accommodation status (being homeless) and having the primary diagnosis of psychosis. Although there is no ideal LOS, current international recommendations advocate for an early discharge as soon as stabilization is successful, with continuation of treatment in less restrictive environments [20]. On the contrary, concerns about prioritizing shorter stay admissions include increasing medical negligence and favouring the revolving door cycle, which can be aggravated with a history of repeated admission and frequent ED visits [20, 21].

Besides the high rates of health services utilization, mental disorders are associated with major social and economic consequences for patients and their families. Patients with mental disorders have high mortality rates [22], poor quality of life [23], lower self-esteem [24], and lack of educational and income-generating opportunities, thus limiting their chances of economic independence and depriving them of social networks and status within the community [14]. Individuals with mental disorders also experience a variety of chronic physical health problems, such as hypertension and cerebrovascular diseases [15]. Despite the pervasive need for mental health treatment among individuals with mental disorders, it is generally acknowledged that many do not use healthcare services [25].

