**Fig. 1 Fig1:**
[figure not shown]
Nova Scotia Health Mental Health and Addictions Program Stepped Care Model

Primary Healthcare Providers (PHP) such as mental health clinicians, nurse practitioners and general practitioners, including those from walk-in-clinics, can refer patients to the service by using the existing central intake pathway. When fully implemented, the program will also welcome walk-in patients who would receive an assessment from a mental health clinician, and if necessary, referred to one of the program psychiatrists for further assessment. Additionally, psychiatrists participating in the program will provide telephone consultations and support for PHPs across the province. All patients accessing the RASP are scheduled to arrive at the clinic 30 minutes before their appointment with the psychiatrists to complete a range of standardized assessments, which are detailed in the section for data collection below. In addition, following the psychiatric consultation, each patient is offered the opportunity to provide feedback about their experience with the RASP provider by completing either a paper-based or an online satisfaction survey. A link for the online satisfaction survey is sent via text message to the patient’s cell phone after the psychiatric evaluation. Additionally, patients can opt-in to participate in an optional Text4Support randomized controlled trial (RCT) where they can either receive daily supportive text messages which are tailored to their primary presenting problem or a single text message which has a link to the NSH/MHAP suite of e-mental health programs [34]. After each psychiatric assessment, a detailed report which covers all essential elements of a comprehensive psychiatric assessment (i.e., presenting complaints, history of presenting complaints, medication history, past psychiatric history, medical and surgical history, family history of mental illness, drug and alcohol history, forensic history, personal history, current social circumstances, pre-morbid personality and a description of the mental status following an examination) is returned to the referring primary care provider within 24 hours. The report includes scores for standardized rating scales and their interpretation and a comprehensive treatment plan based on the biological, psychological and social model. The report encourages the receiving primary care provider to contact the psychiatrist at RASP through the program phone number if they have any follow-up questions. Providers are also advised to re-refer the patient back to the program for further evaluation if the patient's mental health issues are not fully resolved after exhausting the comprehensive treatment plan and recommendations offered. The RASP psychiatrist or a clinical coordinator (mental health clinician) offers each patient information about community resources and support organizations they could utilize in their recovery journey. They are also offered psychoeducation to improve their mental health literacy and information on lifestyle changes that can promote good mental health, such as an increase in physical exercise, good nutrition, avoidance of substance and alcohol abuse and use of self-help resources. Patients with complex presentations or deemed by the RASP psychiatrists to require further psychiatric or mental health support are transferred to the community mental health program for follow-up. In addition, patients accessing the RASP who present an acute risk of harm to themselves or others are transferred to the hospital Emergency Department for further assessment and consideration for inpatient treatment.

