The study seeks to address the following research questions:A.Effectiveness and Impact on Health Services Utilization of the RASP:Did RASP increase the volume of patients referred by PHP? Measured by the number of patients referred by a PHP for a psychiatrist consultation before and after RASP implementation.Did RASP increase the proportion of patients triaged by Central Intake services who had direct access to psychiatric consultations? Measured by the proportion of referrals received by central intake that were booked directly for psychiatry consultation, before and after RASP implementation.Did RASP reduce wait times for access to psychiatrists in the publicly funded MHAP? Measured by the number in calendar days waiting from date referral was received by Central Intake to date patient is scheduled for a psychiatric consultation before and after RASP implementation.Did RASP improve efficiency of the Community Mental Health Programs (CMHP) to address the mental health needs of patients with complex mental health needs? Measured by wait-times for assess to psychiatrists within the CMHP following a referral by a mental health clinician before and after RASP implementation.Did RASP reduce the volume of patients referred by PHP to the ED for a psychiatric consultation? Measured by the number of patients referred by a PHP for a psychiatrist consultation at the ED before and after RASP implementation.Did RASP reduce ED visits, mobile crisis visits, and inpatient mental health services utilization? Measured by the number of mental health and addictions (MHA)-specific ED visits, number of mobile crisis visits, number of MHA-specific hospital admissions, and number in calendar days in LOS for Central Zone patients, before and after RASP implementation.Did patients who attended the RASP and opted to participate in the Text4Support RCT differ in their health services utilization compared to patients who opted not to participate in the Text4Support RCT? Measured by the number of MHA-specific ED visits, number of mobile crises calls, number of MHA-specific hospital admissions, and LOS in calendar days, one-year post-RASP assessment.What are the costs and benefits to Nova Scotia Health from having a RASP for mental health? Measured by the net cost savings associated with RASP considering costs associated with the program and costs saved from avoided high-cost health services utilization (ED visits, mobile crisis visits, and inpatient treatments).B.Perspectives and Experiences of Healthcare Partners and PatientsWhat are healthcare partners' perceptions related to the impact of the RASP on access to community mental health care for patients and support for primary care providers? Measured by qualitative data from key informant interviews with program directors, psychiatrists, primary healthcare providers, MHA service leaders, and representatives from community organizations.What are the patients' perceptions related to their overall experience and satisfaction with the service received? Measured by quantitative and qualitative data from the RASP's satisfaction survey and qualitative data from focus group sessions with a sub-group of the assisted population.C.Population Characteristics and Mental Health MeasuresWhat proportion of patients seen at the RASP continued their treatment with PHP? Measured by the number of patients fully discharged back into the care of their primary healthcare provider with treatment recommendations (chart review data).What proportion of patients seen at the RASP were referred to a community mental health program? Measured by the number of patients referred to a community mental health program by RASP psychiatrists (chart review data).What proportion of patients seen at RASP needed additional psychiatric evaluation at the RASP? Measured by the number of re-referrals to RASP by a PHP.What are the sociodemographic characteristics of the assisted population at program entry? Measured by the frequency and percentages of the sociodemographic characteristics (e.g. age, sex of birth, gender, ethnicity, employment status, source of income, income range, relationship status, family support, housing status, education, provincial zone) (chart review data).What is the status of patients’ recovery and health quality index, and the prevalence of likely major depressive disorder (MDD), likely generalized anxiety disorder (GAD), low resilience, childhood trauma, substance use, and suicide risk at program entry? Measured by patient-completed validated scales scores (chart review data).What is the prevalence of patients' diagnoses made by RASP psychiatrists at program entry? Measured by the frequency and percentages of each psychiatry diagnosis after psychiatry assessment (chart review data).What are the risk factors for ED presentation for mental health concerns and inpatient psychiatric treatments? Measured by Odds Ratios using logistic regression models with sociodemographic and clinical data from the assisted population one year before and after RASP assessment date.

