### Participants and data collection

All RASP patients receive a consent form as part of their intake process, allowing access to their health services utilization records. Only those who sign the consent form will be part of the study. While consent is obtained during the initial assessment for ongoing patient recruitment, data collection is scheduled to commence after the program's first year, in April 2024. Service utilization data will extracted from provincial information systems retrospectively and prospectively at 2-time points: one year pre- and one-year post-assessment date at RASP. In addition, sociodemographic and mental health assessment information, including results from patient-completed validated scales and psychiatry diagnosis, and patient satisfaction will be extracted from routine paper-based initial screening forms. Patient satisfaction quantitative data will be extracted from RASP's patient satisfaction survey, available in a paper-based format and completed immediately after the assessment or REDCap online survey link sent via text message to all patients attending the service just after the assessment appointment.

The control group for the cohort study will comprise patients referred to the MHAP Central Intake Services by a PHP before RASP implementation. The periods for inclusion in the control group will be May 2017 to May 2019 (pre-COVID) and May 2020 to May 2022 (during COVID). By examining the data from these two time points (pre-COVID and during COVID) and comparing them with each other and with data during the RASP implementation period, we will be able to evaluate the impact of the pandemic on health services utilization as well as the impact of RASP implementation in comparison with both the pre-pandemic and during the pandemic periods. Ethics approval for exemption from requiring informed consent for all control group patients has been granted by the Research Ethics Board at Nova Scotia Health (REB file #1028254), allowing control group patients' sociodemographic and health services utilization information from provincial administrative databases to be accessed by the investigators.

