#### Health economic evaluation

We will conduct an economic evaluation through an effectiveness-implementation science lens. Specifically, we will conduct a cost-consequence analysis (CCA) from a Canadian single-payer perspective. The CCA will involve a disaggregated comparison of the costs and benefits (consequences) associated with RASP. The disaggregated analysis reports the intervention effects for the relevant primary and secondary outcomes in their natural units to aid value for money assessments. The study design, population, setting, and location are described elsewhere in this proposal.

We will compare outcomes (ED visits, crisis calls and inpatient days) and costs in the intervention group to the control group. Costing includes costs associated with the pre-implementation, implementation, and ongoing costs. These costs will include space and utilities, new hires specific to RASP, supplies, materials, and equipment, travel costs, volunteer time, and other in-kind donations. We will exclude all research-related costs. These cost data will come from the project documents. In addition, we will collect cost data on health resource use from the case costing centre in the Nova Scotia Health, supplemented with data from the literature if necessary.

Costing will also include costs saved from avoided ED visits, crisis response services and inpatient treatments. Cost analyses will use Nova Scotia Health 2023 costs to ensure relevance to decision-makers. We will estimate the intervention effect for the outcomes using appropriate treatment-effect econometric models with bootstrapping to quantify the uncertainty around the estimates. To enable cost comparisons, the cost of the current models of community-based mental health services, which involve waitlisting of all non-urgent patients (regardless of referral source and reason for referral) to see a mental health clinician as a gateway to receipt of community mental health services, including psychiatry, will be compared with the costs of alternative treatments offered expeditiously through RASP and primary care and community providers. We will compute the net cost savings associated with RASP. Our economic analysis will follow guidelines for economic evaluations, including using probabilistic sensitivity analysis to quantify the uncertainty around the implementation costs [48].

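### As worded, the pre/post comparison attaches whole-stay LOS to admissions in each year, which counts the two windows unequally and can shift inpatient days by about as much as the hypothesised 10%

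*Protocol article*

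**What the plan says.** In the Protocol article, Outcome measures lists among the primary outcomes the mean differences in frequency, duration and cost of "hospital admissions and readmissions and associated LOS for each admission) between one year pre- and post-assessment date for same patients at RASP".

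The only definition of LOS is in the Background, where it is introduced as a quality-of-care indicator: "LOS is defined as the number of days between admission and discharge dates for each admission experienced".

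Participants and data collection sets the time points for extracting utilization data as "one year pre- and one-year post-assessment date at RASP". The programme description under Fig. 1 makes day 0 an outpatient attendance: "All patients accessing the RASP are scheduled to arrive at the clinic 30 minutes before their appointment with the psychiatrists".

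The Hypothesis section expects at least a 10% reduction in high-cost utilization, in the within-subject as well as the between-subject comparison.

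The article does not say whether a stay that crosses a window edge is cut there. Nor does it say whether a whole stay belongs to the year of its admission or of its discharge. Details of the variables are referred to Table S2, which is not shown.

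**The concern.** The plain reading of the outcome is to find the admissions in each year and give each its full admission-to-discharge LOS. Read this way, a patient admitted on day +350 and discharged on day +410 scores 60 post-year days, although only 15 of them lie in the post-year. The pre-year cannot have such a tail, because the patient walks into the clinic on day 0. At its far end, a stay that began before day −365 and ran into the pre-year is attached to no pre-year admission and drops out.

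Assigning whole stays by discharge date reverses the imbalance. The pre-year then takes in full stays that began before it, and the post-year loses stays still open at its end.

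A within-subject comparison has no control arm to absorb this. An artefact near 10% could hide the hypothesised reduction. Under discharge-date assignment it could imitate one, which would be the more harmful error.

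**Working it through.** **Plan's own figure.** The article states no mean, SD or distribution of LOS and no expected number of inpatient days, so there is no plan figure to reproduce.

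**Inputs.** From the article: window W = 365 days on each side, patient out of hospital on day 0, LOS = admission to discharge, target reduction 10%. Assumed: constant admission rate r with no true change, mean LOS m of 10, 20 or 30 days, and SD equal to the mean (CV 1).

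**Formulas.** A pre-year stay of length L must end by day 0, so it can start on only W − L of the W days. A post-year stay can start on any day.
- Admission date: pre = r·E[L(W − L)], post = r·W·E[L]. Hence post/pre ≈ 1/(1 − m(1 + CV²)/W), which at CV 1 is 1/(1 − 2m/365).
- Discharge date: the roles swap, so post/pre ≈ 1 − 2m/365.

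**Total inpatient days, no true change, CV 1:**

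| Mean LOS | Admission date, formula | Simulated | Discharge date, formula | Simulated | Days cut at edges, simulated |
|---|---|---|---|---|---|
| 10 d | 1/(1 − 20/365) = 1.058 | +6.5% | 0.945 | −4.7% | +0.7% |
| 20 d | 1/(1 − 40/365) = 1.123 | +12.0% | 0.890 | −11.1% | −0.2% |
| 30 d | 1/(1 − 60/365) = 1.197 | +19.7% | 0.836 | −16.3% | +0.1% |

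The simulation followed 1,000,000 patients per scenario alternating between community and hospital (0.2 admissions per year), keeping those out of hospital on day 0. The non-zero values in the last column are Monte Carlo error.

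**Mean LOS per admission, admission date.** The pre-year mean is m(W − 2m)/(W − m), so post/pre = (W − m)/(W − 2m):
- 10 days: 355/345 = 1.029 (simulated 9.71 and 10.03 days, +3.3%)
- 20 days: 345/325 = 1.062 (18.86 and 19.98 days, +5.9%)
- 30 days: 335/305 = 1.098 (27.27 and 30.02 days, +10.1%)

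The rest of the rise in total days comes from the number of admissions. At 20 days this is 365/345 = 1.058, and 1.058 × 1.062 = 1.12.

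**Against the target.** At a mean of 20 days, a true 10% fall in total days would appear under admission-date assignment as 0.90 × 1.123 = 1.01, that is, no reduction. Under discharge-date assignment, no effect at all would appear as an 11% fall.

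**Sensitivity, admission date.** At a mean of 20 days the rise is 5.8% with CV 0, 7.3% with CV 0.5, 21.7% with CV 1.5 and 37.1% with CV 2. It is 1.4% for a fixed 5-day stay and 62.8% for a mean of 30 days with CV 2.

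**The case against.** The strongest reply is that the Methods never say stays are left uncut. The admission-to-discharge definition sits in the Background with a literature citation, the one-year extraction is equally compatible with counting only in-window days, and Table S2 may hold a rule. This stands in part: a reader might infer that the plan has fixed an uncut count, and it has not. But the outcome is worded as LOS attached to each admission, and the only definition supplied is the whole stay. The text as written therefore points to a measure that is biased under either assignment date.

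A reader might also infer that the comparison must show a rise, of a known size. The article does not support that. The direction depends on an assignment date it does not give, and the size rests wholly on assumed LOS values. The constant admission rate is also a simplification, since the programme description says patients at acute risk are transferred from RASP to the ED for consideration of admission.

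A third inference would be that the RASP/control contrast is biased too. Under Quantitative analysis both arms are indexed on an attended appointment, with the same pre- and post-years, so any edge rule acts on both. No bias there has been shown.

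Two further places lend no direct support. The research question on "number of MHA-specific hospital admissions, and number in calendar days in LOS for Central Zone patients, before and after RASP implementation" is framed around programme launch, when patients need not be out of hospital. The economic section's "We will compare outcomes (ED visits, crisis calls and inpatient days) and costs in the intervention group to the control group" is a between-group comparison and already names inpatient days.

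Finally, cutting at the edges is not the only neutral rule: counting every overlapping stay in full also gave about 0% (−0.1% to +0.7% at CV 1). It does, however, count days outside the year being compared.

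**Conclusion.** The concern holds for the within-subject comparison of inpatient duration and of any inpatient cost built on it. Whole-stay LOS assigned to a year by one of its end dates is not counted alike before and after an outpatient index visit. The direction is a rise or a fall according to which date is used.

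The quoted sizes (about 6–20% up or 5–16% down in total days, and about 3–10% in mean LOS per admission by admission date) are conditional on a mean LOS of 10 to 30 days, CV 1 and a stable admission rate. They show that the artefact can match the hypothesised 10%; they do not predict what this study will find. Short, uniform stays would make it minor.

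**What to change.** In Outcome measures, define the pre/post inpatient-duration outcome as the number of inpatient days falling inside each 365-day window. Split any stay that crosses a window edge at that edge, count a stay still open at the end of the post-year up to the window end, and include the in-window days of stays begun before day −365. Base the pre/post inpatient cost on the same days. Report admission-to-discharge LOS per admission as a supplementary measure, stating which date assigns a stay to a year. If Table S2 already contains such a rule, align Outcome measures with it.

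The cost is about one sentence. LOS on the article's own definition already needs both admission and discharge dates. The one added demand is that the extraction must also pick up stays that began before the pre-year.
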